#### GPs

We do not anticipate a high drop-out rate of GPs, as the demands on GPs are not onerous. As patients are consented separately to GPs, patients can continue even if their GPs withdraw from the study.

### Statistical analyses

All surveys collected on laptop computers will be downloaded to a central database. Where necessary in the analysis, the longitudinal and hierarchical/cluster nature of the study design will be taken into account using mixed effects models and other appropriate methods (see below). The primary analysis will be by intention to treat. Analyses will address the following questions:

#### Do GPs trained in the use of a screening instrument detect dementia better?

Detection rates of GPs trained in using the GPCOG (the Intervention group) will be compared with detection rates of Waitlist GPs against the 'gold standard' of the CAMCOG.

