#### Intervention GPs

Intervention GPs will participate in two visits at their surgery with a peer medical or nurse educator. At the first visit (after completion of the baseline audit), GPs will be taught how to use the GPCOG screening instrument (described below), and will be given information about dementia diagnosis, diagnostic workup and management according to strategies incorporated in the RACGP Consensus Guidelines for the care of Patients with Early Dementia (hereafter called the RACGP Dementia Guidelines) [19]. Negative attitudes about making a dementia diagnosis will be explored and addressed. With the GPs' consent, these sessions will be recorded for qualitative analysis. The structural issue of lack of time in the GP consultation will be addressed by teaching the GPs to use a brief screening instrument and by discussing potential methods of obtaining assistance from the practice nurse. A business case regarding the cost effectiveness of dementia assessment will also be presented. All intervention GPs will be provided with support materials and the RACGP Dementia Guidelines at this visit. These GPs will receive a second detailing visit after completion of their 12 month audit. At the second visit, intervention GPs will receive written and verbal feedback about their baseline audit in the light of individual patient results from the home assessment.

As the study is being conducted across five sites, a number of different peer educators will be used. All educators will undergo a training program either face-to-face or via teleconference to familiarise them with the educational package developed for intervention GPs. The package consists of a slide presentation that will be delivered by educators via laptop computer, and hard-copy support materials that will be supplied to the GPs.

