#### GP audit

GPs will be sent a list of their participating patients by fax or email. They will be asked to confirm each patient's eligibility for the study and to provide their clinical judgement in relation to each patient's dementia status using one of four options: No Dementia, Possible Dementia, Probable Dementia or Definite Dementia. GPs will be asked to complete a supplementary audit for any patients with possible, probable or definite dementia to gather data on differential diagnosis (e.g depression), memory-related tests and investigations performed (i.e. paper and pencil test; pathology; radiology) and referrals to services and specialists. GPs will return their completed audit forms to local project officer via mail, fax or email. GPs will complete audits at baseline, 12 and 24 months.

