### Outcome measures

Primary outcome measures related to the first aim (collected at baseline, 12 months and 24 months) are:

1. World Health Organization Quality of Life-Bref Scale (WHOQOL-BREF) score for patients

2. Geriatric Depression Scale score for patients

Secondary outcome measures related to the first aim (collected at baseline, 12 months and 24 months) are:

1. World Health Organization Quality of Life-Bref Scale (WHOQOL BREF) for carers

2. Beck Depression Inventory score for carers

3. Agreement of GP audit for dementia with CAMCOG instrument

4. GP differential diagnosis for dementia

5. GP identification and treatment of reversible causes of dementia 6.GP dementia related referrals made

7. General Practice Assessment Questionnaire score

8. Acceptability of the process scale score

9. Services accessed

To meet the second aim of the study, screening and case finding groups (as defined above) will be compared on primary and secondary outcome measures 1 and 2 as listed above. The GPCOG score will be compared with the gold standard of the CAMCOG score to address the third aim of the study. The performance of the GPCOG against the CAMCOG will also be compared with that of the MMSE against the CAMCOG, as the MMSE is widely used to screen for dementia.

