### Sample size

It was calculated that 45 patients with dementia in each group (Waitlist and Intervention) would give a power of 0.9 to detect a 7% difference between the change in pre and post scores on any of the four domain scales of the WHOQOL-BREF with a type 1 error of .05. The population standard deviation used is 18.5 [32] and the Pearson correlation coefficient between the pre and post scores for both groups is assumed to be 0.7, based on pilot data available from the University of Melbourne.

The hierarchical nature of the study design will probably lead to some within cluster correlations and the greatest impact of this is likely to be associated with patients clustered within a GP practice. Clustering within each GP may be discounted, as it is anticipated that most GPs will have less than five patients with dementia in this study. Assuming an intra-class correlation coefficient of 0.05 and an average cluster size of 5 patients with dementia in a practice, this gives a design effect of 1.45 and a total sample size of 54 patients per group. We will therefore allow for 56 patients with dementia in the waitlist group and 112 in the intervention group to allow for comparison of outcomes between the waitlist and intervention groups overall. This sample size also allows comparison of "case finding" and "screening" patients and their support persons within the group. It is assumed that about 50% of participants will be screening and 50% case finding. Thus, we aim to recruit 168 participants with dementia overall. Based on a dementia prevalence of approximately 10% in over 75 year old Australians [37], we aim to recruit a total of 2,000 participants.

For the GDS, following the same set of assumptions and approach as for the WHO QOL-BREF (power, type 1 error and correlations), 45 patients in both the Intervention and Waitlist groups would allow detection of an average difference in the change in pre and post scores of 0.9 points on the 15 point GDS, using a standard deviation of 2.39 [28]. The cluster effect would be the same as for the WHOQOL-BREF.

For an estimate of test re-test reliability on the GPCOG a sample size of 100 will be used to ensure the correlation is estimated to a reasonable precision. The 95% confidence interval for a Pearson correlation of 0.9 would be [0.86, 0.93] and for a correlation of 0.80 [0.73, 0.85].

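### The GP detection comparison does not commit to using each patient's baseline audit rating, a near-free gain in precision for aim 1(i)

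*Protocol article*

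**What the plan says.** The section asking whether trained GPs detect dementia better gives one sentence of analysis: "Detection rates of GPs trained in using the GPCOG (the Intervention group) will be compared with detection rates of Waitlist GPs", with the CAMCOG as reference. It names no time point, no audit category that counts as detection, and no role for the baseline audit.

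The matching endpoint under Outcome measures is secondary outcome 3, "Agreement of GP audit for dementia with CAMCOG instrument", collected at baseline, 12 and 24 months. The opening of Statistical analyses adds that, where needed, "the longitudinal and hierarchical/cluster nature of the study design will be taken into account using mixed effects models and other appropriate methods".

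The data for a baseline-adjusted analysis are already planned. Under GP audit, each GP rates each participating patient "using one of four options: No Dementia, Possible Dementia, Probable Dementia or Definite Dementia", and "GPs will complete audits at baseline, 12 and 24 months". Under Intervention GPs, the order is fixed: "At the first visit (after completion of the baseline audit), GPs will be taught how to use the GPCOG screening instrument". The rating therefore exists in both arms before any education.

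**The concern.** Aim 1(i) asks whether training improves identification. Among patients in the CAMCOG dementia range, some will already carry a GP rating of dementia at the baseline audit. If they keep it, they count as detected in either arm and add nothing to the contrast. They pull both rates up by the same amount and narrow the gap between them. Chance differences between practices in how many patients were already known also stay in the error term.

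The protocol recognises the distinction elsewhere. The baseline audit helps define case-finding patients, and the case-finding versus screening analysis asks how many diagnoses would have been missed without the GPCOG. That analysis is confined to the Intervention group. For the between-arm comparison the article does not commit to using the rating. A real gain among previously missed patients could then be harder to demonstrate than it needs to be.

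**Working it through.** **The plan's own figure.** There is none to reproduce. The Sample size section covers WHOQOL-BREF and GDS change and GPCOG reliability; it states no detection rate, target difference or power for detection.

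**Inputs from the article.** 56 waitlist and 112 intervention patients with dementia (Sample size); 180 at 12 months, about 60:120 at the 2:1 allocation (Study drop outs/withdrawals); "with a type 1 error of .05", taken as two-sided; ICC 0.05 and 5 patients per practice, giving 1 + (5 − 1) × 0.05 = 1.20. The article prints 1.45 for that design effect, which is a separate matter; 1.20 is what its inputs give.

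**Assumed, because the article gives no figure.** Share already identified at baseline, b, from 0.1 to 0.7. New detection among the rest, c0 (waitlist) v c1 (intervention): 10% v 30%, 10% v 40%, 20% v 40%, 20% v 50%. Already-identified patients stay identified.

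**Step 1, dilution.** The all-patient rates are b + (1 − b)c0 and b + (1 − b)c1, so the difference is (1 − b)(c1 − c0). A 20-point difference becomes 12 points at b = 0.4 and 8 points at b = 0.6.

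**Step 2, power.** Power = Φ[(d − 1.96·SE0)/SE1], where SE0 is the pooled standard error under no difference and SE1 the unpooled one. Take b = 0.4, 10% v 30%, 56:112 and design effect 1.2, so effective numbers are 46.7:93.3.

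- All patients: 0.46 v 0.58, d = 0.12, SE0 = 0.0894, SE1 = 0.0891. Power = Φ[(0.12 − 0.175)/0.0891] = Φ(−0.62) = 0.27.
- Not identified at baseline: 0.10 v 0.30, effective 28:56, d = 0.20, SE0 = 0.0979, SE1 = 0.0835. Power = Φ[(0.20 − 0.192)/0.0835] = Φ(0.10) = 0.54.

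**Step 3, other values** (56:112, design effect 1.2):

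| New detection | b | All patients | Not identified at baseline |
|---|---|---|---|
| 10% v 30% | 0.2 | 0.45 | 0.68 |
| 10% v 30% | 0.4 | 0.27 | 0.54 |
| 10% v 30% | 0.6 | 0.17 | 0.37 |
| 20% v 50% | 0.2 | 0.77 | 0.89 |
| 20% v 50% | 0.4 | 0.55 | 0.78 |
| 20% v 50% | 0.6 | 0.35 | 0.59 |

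Over the full grid at 60:120, with design effect 1.0 or 1.2, the relative loss runs from about 3% (10% v 40%, b = 0.1, no clustering: 0.961 v 0.992) to 58% (10% v 30%, b = 0.6, no clustering: 0.199 v 0.468). At b of 0.2 or less it is 3% to 34%.

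**Step 4, does adjustment without restriction recover it?** A simulation with 47:93 effective patients (20,000 runs per setting) at b = 0.4 and 10% v 30% compared the plain test, a test of all patients stratified by baseline rating, and the restricted test. With no reversals, power was 0.29, 0.56 and 0.56. If 10% of already-identified patients lose the rating, it was 0.28, 0.42 and 0.56, so stratification then regains about half of the gap.

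**The case against.** The strongest reply is that the article has not chosen an unadjusted analysis. The sentence states a question and names no model, and the paragraph above it promises mixed models for longitudinal and clustered data. Since the outcome is measured at baseline too, such a model could bring the baseline audit in. Covariates are also commonly left to an analysis plan, which is not shown. This stands to the extent that a reader who infers a fixed plan for a raw rate comparison goes beyond the text. What remains is that the general promise applies only where needed and does not commit this comparison to the baseline rating.

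A reader might also infer that most of the power is lost. The documents do not support that: they give neither the share already known nor any detection rate, and the loss passes half in only part of the assumed range.

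Nor does the text establish that already-identified patients form an identical block in both arms. That assumes no reversals and counts a rating of possible dementia as detected. If detection means probable or definite, training could still move patients rated possible.

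Finally, it is tempting to make patients not identified at baseline the headline population. The audit precedes training, but the article does not show that it precedes allocation. Practices are allocated once a GP consents, patients are then recruited by mail, and GPs audit the resulting list. Only the interviewers are described as blind. Figure 1 is not available to settle the order. Restricting could select on a rating made by GPs who know their arm, and it changes the question from overall to new detection.

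**Conclusion.** The point holds as an improvement in precision. The stated comparison does not commit to a rating that is collected in both arms before training, and pooling already-identified patients shrinks the arm difference by (1 − b). The cost in power is real but cannot be fixed from the documents: about 3% to 58% in relative terms under the assumptions shown, with 0.27 v 0.54 as one mid-range example.

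The ICC of 0.05 was set for quality of life. One for GP audit behaviour could be larger and would lower power in both analyses. Detection is secondary and unpowered, so nothing stated is contradicted, and the primary outcomes are unaffected.

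**What to change.** In the section on whether trained GPs detect dementia better, specify:

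1. 12-month identification in all patients in the CAMCOG dementia range, analysed with a mixed model that contains the patient's baseline GP audit rating, a random effect for practice, and the randomisation strata (site and practice size).
2. Which of the four audit categories count as detected.
3. As a supporting analysis, the arm difference among patients not identified at the baseline audit.
4. The unadjusted rates by arm beside both.

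It would also help to state whether the baseline audit is completed before or after practice allocation, because this determines how far results conditioned on it can be relied on.

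The cost is wording only, since the audits are already planned. Settle it before outcome data by arm are examined.

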#### Do GPs trained in screening and management distinguish dementia from other conditions, particularly depression, compared with a waitlist group?

Differential diagnoses (particularly of depression), of the Intervention group will be compared with those of the Waitlist group. Misclassification rates of the GPs in the Intervention group will be compared with those in the waitlist group.

#### Do GPs trained in screening and management adhere to the guidelines?

Outcomes measured will include identification of reversible causes of dementia, tests ordered and referral patterns to specialists, support services and Alzheimer's Australia, as suggested in the guidelines.

#### Do GPs trained in screening and management provide better health outcomes?

Outcomes of Intervention and Waitlist groups will be compared at twelve months, for both patients and their carers (quality of life, depression, satisfaction with care, services accessed)

#### Do subjects with and without dementia and support persons find the screening acceptable?

All subjects and support persons will be asked to rate the acceptability of the screening instrument and procedures. Descriptive analysis will be performed. Case finding and screening groups will be compared.

#### Do GPs find the process acceptable?

GPs will be asked to rate the acceptability of the GPCOG and the Management Guidelines. Descriptive data will be reported.

#### Does case finding or screening produce better results?

Within the Intervention group, the patient outcomes for the group with memory complaints or identified by the GP as having possible or probable dementia (case finding group) will be compared with outcomes for the group without memory complaints or identified memory problems (screening group). Acceptability of the process and satisfaction with care will be particularly examined, both from a quantitative and a qualitative point of view. The performance of the GPCOG in the case finding and screening groups will be compared. In particular positive predictive value, negative predictive value and misclassification rates will be compared. GP audits will be examined to determine how many patients in each group would have a missed diagnosis of dementia if the GPCOG had not been administered.

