### Screening vs case finding as a means of identifying dementia

In general, medical advisory groups and policy makers recommend case finding (further testing only for those who are perceived by the GP as having symptoms suggesting possible dementia) rather than broadly screening persons over a certain age for dementia [20,21]. It is thought that screening in this low prevalence population would result in false positives, causing distress to the patient and their support person, as well as being a burden to the healthcare system. Other guidelines have withheld judgment as they claim insufficient evidence for or against screening [21,22]. This study will compare screening and case finding approaches to identifying dementia.

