### Aims of the study

1. Compared to a GP group which does not receive peer delivered education, to examine whether training in and use of a dementia screening instrument and relevant information (see *The Intervention *section below) improves:

i. GP identification (diagnosis) of dementia

ii. Distinction by GPs between dementia and other diseases, including depression (hereafter termed "differential diagnosis")

iii. GP elimination of reversible causes of cognitive impairment

iv. Active management of dementia by GPs as evidenced by increased referral to appropriate services, to Alzheimer's Australia and/or to medical specialists for memory problems where indicated.

Outcomes for consumers and their support people in terms of quality of life (primary outcome), depression (primary outcome), satisfaction with care, and access to Alzheimer's Australia, appropriate services or specialists when indicated.

2. To determine whether a screening or a case finding approach to dementia results in:

i. better outcomes for people with dementia and their carers

ii. a more acceptable process for consumers, support people and GPs

3. o test the psychometric properties of the GPCOG including inter-rater reliability, test-retest reliability and comparison with the MMSE..

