### Recruitment of participants

#### GPs

With the exception of Bendigo (which will also include nearby towns as noted above) each site will generate a list of possible GP practices within 30 km of the site headquarters based on lists provided by the local Division of General Practice. Practices will be allocated a random approach order, and will be contacted via phone initially. GPs who express an interest in participation will be visited in order for the study to be explained. Basic demographics will be collected at this visit, from those GPs that agree to participate. It is not expected that all the GPs in a practice will participate. When one or more GPs in a practice consent, the practice as a whole will be allocated to either the intervention or waitlist group. Randomisation will occur at a practice level in order to avoid contamination from patients visiting several GPs who had been randomised to different arms within a single practice.

Randomisation will follow procedures outlined in the CONSORT statement [27]. Practices will be allocated in a ratio of 2:1 to the Intervention or Waitlist group, using an allocation schedule provided independent of the study team, by the Centre for Epidemiology and Biostatistics at the University of Newcastle. The randomisation code has been developed using a computer random number generator to select random permuted blocks. Block lengths of 3 or 6 will be varied randomly. Practices will be stratified by site, and by size of practice as either standard or large (large = more than 7 GPs working in the practice). The intervention group will be kept at twice the size of the waitlist group in order to have sufficient power to compare the effects administering the GPCOG on case finding versus screening patients (see explanation below).

Inclusion criteria for GPs/practices

• Located within 30 kilometres of recruitment centre (with the exception of Bendigo, a rural town)

• Consent to participate in study

• Have patients on a computerised database

• Have patients aged 75 years and over and living in the community

• Consent to being randomised to either intervention waitlist group.

Exclusion criteria for GPs/practices

• Involved in project development

• Does not meet inclusion criteria

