### Case finding and screening

"Case finding" patients will be identified during the patient interview using the following 4 questions:

1. Do you have any complaints about your memory?

2. Have you mentioned these to you GP?

3. If not, have you been intending to tell your GP?

4. Have you sought treatment or taken any remedies such as herbal medications or vitamins specifically for you memory? Please give details.

If questions 2, 3 or 4 are answered in the affirmative, the patient will be considered as a "case finding" patient. Patients identified as having possible or probable dementia on the GP baseline audit will also be considered as a "case finding" patient. All other patients will be identified as "screening" patients - that is, patients who would not receive a cognitive function test unless the GP decided to screen all patients aged over a certain age.

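### Aim 2i (outcomes): the planned case-finding versus screening contrast compares two non-randomised patient types inside the Intervention arm, so it cannot be read as an effect of one approach against the other

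*Protocol article*

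**What the plan says.** - **The question.** Aims of the study, aim 2: "To determine whether a screening or a case finding approach to dementia results in" better outcomes for people with dementia and their carers (2i) and a more acceptable process (2ii).
- **Case finding as a strategy.** The Background section on screening versus case finding describes it as "further testing only for those who are perceived by the GP as having symptoms suggesting possible dementia", as opposed to testing everyone above a certain age.
- **Case finding as a patient type.** Under Case finding and screening: "If questions 2, 3 or 4 are answered in the affirmative, the patient will be considered as a 'case finding' patient". A second route follows: "Patients identified as having possible or probable dementia on the GP baseline audit will also be considered as a 'case finding' patient". Then: "All other patients will be identified as 'screening' patients". A yes to question 1 alone (any memory complaint) does not place a patient in the case finding group.
- **What is randomised.** Practices, 2:1, to Intervention or Waitlist (Recruitment of participants, GPs). The reason given for the ratio is the type comparison: "The intervention group will be kept at twice the size of the waitlist group in order to have sufficient power" for comparing the effects of giving the GPCOG in the two types.
- **Who is tested.** The Abstract has Intervention GPs giving the GPCOG to consenting patients. Under Patient assessment, the letter handed to Intervention patients asks them to see their GP and have the GPCOG repeated, whatever their type. The research nurse also gives the GPCOG to consenting patients in both arms.
- **The analysis.** Does case finding or screening produce better results?: "Within the Intervention group, the patient outcomes for the group with memory complaints" or GP-identified possible or probable dementia are compared with those of the remaining Intervention patients. The same section plans acceptability, satisfaction and GPCOG predictive values by group, and will use GP audits to determine "how many patients in each group would have a missed diagnosis of dementia if the GPCOG had not been administered".
- **The outcomes.** Outcome measures lists patient WHOQOL-BREF and GDS, and carer WHOQOL-BREF and Beck scores, for this comparison.

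**The concern.** The aim concerns two policies for deciding whom to test. The analysis compares two kinds of patient under one policy. No practice or patient is assigned to a case-finding-only policy, and within the Intervention arm both types are offered the same thing.

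Patients who have raised memory problems, sought remedies or been suspected by their GP plausibly differ from the rest in cognition, mood, quality of life and carer burden, and in how these develop. Those are the outcomes to be compared. The result could be reported as evidence for or against screening when it shows only that the two kinds of patient differ, or it could hide a real effect. More patients would not cure this.

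The missed-diagnosis analysis has a related difficulty. The baseline audit is the one completed before the GP is taught the GPCOG, and the grouping rule has already used it to take patients rated possible or probable out of the screening group.

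**Working it through.** **1. Sources of a difference with no effect of approach.** Within the Intervention arm, the contrast is (case-finding type) minus (screening type).
- On follow-up scores, any stable baseline gap carries through in full. As an assumption, a gap of 0.3 to 0.5 SD with the protocol's SD of 18.5 is 0.3 × 18.5 = 5.6 to 0.5 × 18.5 = 9.3 points, against a planning difference of 7.
- On change scores, a stable gap cancels. Bias then requires the types to differ in natural course.
- Baseline adjustment within the arm does not make the types exchangeable, because membership was never randomised.

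**2. How often a differing natural course would look like an effect.** Inputs from Sample size: SD 18.5, pre-post correlation 0.7, 112 Intervention patients with dementia, split about 50:50, so 56 v 56.
- SD of change = 18.5 × √(2 × (1 − 0.7)) = 14.33.
- Design effect = 1 + (5 − 1) × 0.05 = 1.20. The protocol prints 1.45, but its 54 per group is 45 × 1.20; 45 × 1.45 would be 65.
- SE = 14.33 × √(1.20 × 2/56) = 2.97.

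Probability of two-sided significance at 0.05, for an assumed difference in natural change:

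| Assumed difference (points) | Probability |
|---|---|
| 0 | 0.05 |
| 2 | 0.10 |
| 4 | 0.27 |
| 7 | 0.66 |

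**3. The protocol's own sample size.** The standard two-sample formula on change scores (7 points, SD 14.33, two-sided 0.05, power 0.90) gives 89 per group, not the stated 45. A one-sample formula gives 45. That is a separate matter and nothing here depends on it, except that the section's statement that the sample allows this comparison is weaker than it looks: 56 v 56 has power 0.66 on change scores at design effect 1.20.

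**4. Can the Waitlist arm be classified in the same way?** Yes. The four questions are part of an interview by staff blind to allocation (Patients and support persons), all GPs complete the baseline audit (The intervention), and the first education visit follows that audit (Intervention GPs).

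**5. Precision of a two-arm analysis.** With 56 Waitlist patients with dementia split 50:50, there are 28 per type, against 56 per type in the Intervention arm.
- Baseline-adjusted SD = 18.5 × √(1 − 0.7²) = 13.21.
- Within-type effect: SE = 13.21 × √(1.20 × (1/56 + 1/28)) = 3.35; 95% half-width 1.96 × 3.35 = 6.6 points.
- Interaction: SE = 3.35 × √2 = 4.74; half-width 1.96 × 4.74 = 9.3 points.
- Power for a 7-point interaction: 0.31 baseline-adjusted. On change scores the SE is 14.33 × √(1.20 × (2/56 + 2/28)) = 5.14 and power is 0.28.

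The design effect of 1.20 is carried over unchanged from the whole-arm calculation, so these are approximations.

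**6. Missed diagnoses.** GP audit lists four ratings: no, possible, probable and definite dementia. The rule moves possible and probable to case finding. Dementia cases left in the screening group are therefore those rated no dementia, plus any rated definite, which the rule does not mention. A missed-diagnosis proportion there is close to fixed by definition. The number of such patients is not.

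**The case against.** Several objections have force.

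- **Aim 2 as a whole.** A reader might infer that aim 2 cannot be addressed at all. The document does not support that. Aim 2ii is about acceptability, which the analysis section singles out for quantitative and qualitative study. How patients with and without a prior prompt experience testing, and how the GPCOG performs in each type, is useful description. The point is confined to 2i.
- **The Waitlist arm as the answer.** A reader might infer that bringing in the Waitlist arm would settle screening against case finding. It would not. The randomised contrast is the whole package of education, guidelines, GPCOG and audit feedback, and its interaction with type is effect modification. Because the nurse gives the GPCOG in both arms, Waitlist patients are not untested either.
- **Exposure.** A reader might infer that every Intervention patient received the GPCOG from the GP. The document shows only that this was planned and that patients were directed to it by letter.
- **Circularity.** A reader might infer that the missed-diagnosis analysis is worthless. It asks how many patients, and the count in the screening group is the potential extra yield of screening. Regrouping on questions 2 to 4 alone is no remedy, since it would discard GP suspicion, which is the Background's own definition of case finding.
- **Level of detail.** Model terms usually belong in an analysis plan, and Statistical analyses already foresees mixed models. Outcome measures states the group comparison without restricting it to one arm. But neither adds a randomised contrast, and the section on this question fixes both the analysis set and the comparator. The point is what is stated, not what is left out.

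**Conclusion.** The point stands for aim 2i. The planned within-Intervention comparison of patient, depression and carer outcomes describes differences between patient types and cannot be read as an effect of screening versus case finding. This follows from the design and needs no numerical assumption.

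The size of the bias cannot be derived from the document. The probabilities of 0.10 to 0.66 rest on assumed differences in natural change of 2 to 7 points and on the protocol's SD, correlation and 50:50 split. The 5.6 to 9.3 point follow-up gap rests on an assumed baseline difference of 0.3 to 0.5 SD that persists unchanged.

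The two-arm analysis is a partial but real improvement. It gives a randomised estimate in the patients whom screening would add, though an imprecise one. The conclusion should not be stretched to acceptability, to GPCOG accuracy by type, or to the count of missed diagnoses.

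**What to change.** 1. For aim 2i, specify a two-arm, baseline-adjusted mixed model allowing for practice, with arm, patient type and arm-by-type terms. Report the Intervention-versus-Waitlist effect within each type with its interval, and the interaction.
2. Label the within-Intervention comparison of outcomes descriptive.
3. State that the model estimates the effect of the education and GPCOG package by patient type, not one strategy against the other, and that the nurse gives the GPCOG in both arms.
4. State the expected precision, so that a non-significant interaction is not reported as equivalence of the two approaches.
5. Keep acceptability, predictive values and misclassification by type as descriptive analyses.
6. Report missed diagnoses in the screening group as a count, not as a rate compared between groups, and say how patients rated definite at baseline are classified.

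The cost is analysis wording only, since the data are collected in both arms. The price is wide intervals: about 28 Waitlist patients with dementia per type, and low power for the interaction.
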